## Abstract

**Background:**

It is estimated that around 15–30% of patients with early stage colon cancer benefit from adjuvant chemotherapy. We are currently not capable of upfront selection of patients who benefit from chemotherapy, which indicates the need for additional predictive markers for response to chemotherapy.

It has been shown that the consensus molecular subtypes (CMSs), defined by RNA-profiling, have prognostic and/or predictive value. Due to postoperative timing of chemotherapy in current guidelines, tumor response to chemotherapy per CMS is not known, which makes the differentiation between the prognostic and predictive value impossible. Therefore, we propose to assess the tumor response per CMS in the neoadjuvant chemotherapy setting. This will provide us with clear data on the predictive value for chemotherapy response of the CMSs.

**Methods:**

In this prospective, single arm, multicenter intervention study, 262 patients with resectable microsatellite stable cT3–4NxM0 colon cancer will be treated with two courses of neoadjuvant and two courses of adjuvant capecitabine and oxaliplatin. The primary endpoint is the pathological tumor response to neoadjuvant chemotherapy per CMS. Secondary endpoints are radiological tumor response, the prognostic value of these responses for recurrence free survival and overall survival and the differences in CMS classification of the same tumor before and after neoadjuvant chemotherapy. The study is scheduled to be performed in 8–10 Dutch hospitals. The first patient was included in February 2020.

**Discussion:**

Patient selection for adjuvant chemotherapy in early stage colon cancer is far from optimal. The CMS classification is a promising new biomarker, but a solid chemotherapy response assessment per subtype is lacking. In this study we will investigate whether CMS classification can be of added value in clinical decision making by analyzing the predictive value for chemotherapy response. This study can provide the results necessary to proceed to future studies in which (neo) adjuvant chemotherapy may be withhold in patients with a specific CMS subtype, who show no benefit from chemotherapy and for whom possible new treatments can be investigated.

**Trial registration:**

This study has been registered in the Netherlands Trial Register (NL8177) at 11–26-2019, https://www.trialregister.nl/trial/8177. The study has been approved by the medical ethics committee Utrecht (MEC18/712).

## Background

Colon cancer is one of the most common types of cancer in the Netherlands with an incidence of around 9.800 patients in 2018 [1]. Approximately 80% of patients present with local disease (stage I-III). Curative surgery followed by adjuvant systemic chemotherapy is standard of care in patients with microsatellite stable (MSS) high-risk stage II and stage III colon cancer. Despite this intensive treatment, 20–30% of the patients develop metastatic disease. These patients do not benefit enough from the current adjuvant systemic therapy. Moreover, it is estimated that 50% will not develop metastases after surgery alone and are therefore over-treated with adjuvant chemotherapy. Identifying the patients at risk of developing metastases, as well as those responding to therapy is a clear unmet need in colon cancer care. The development of new prognostic and predictive markers for chemotherapy response is therefore of utmost importance.

Many efforts have been undertaken to stratify CRC patients into biologically and clinically distinct subtypes. One of these led to the development of the Consensus Molecular Subtypes (CMSs), which is based on RNA expression profiling of tumor tissue and which is currently considered to be the most robust molecular stratification in CRC [2]. CMS1 is characterized by hypermutation, microsatellite instability (MSI) and strong immune infiltration. CMS2, the canonical subtype, has marked WNT and MYC signaling activation. CMS3 is enriched for *KRAS*-mutations and shows evident metabolic deregulation. CMS4, the mesenchymal subtype, is characterized by prominent TGF- activation, stromal invasion and angiogenesis activation. Subtyping in a large heterogeneous patient cohort (*n* = 2.129) with stage I to IV colorectal cancer showed significant differences in prognosis, with CMS4 as the poor-prognosis subtype, confirming the clinical relevance of the intrinsic processes implicated in each CMS [2].

These results support the idea that the CMSs might have predictive value for response to chemotherapy. Due to the postoperative timing of chemotherapy in current guidelines, the tumor response to chemotherapy is not assessable, which makes a distinction between the prognostic value and predictive value of the subtypes impossible. Only a randomized controlled trial in which patients would be randomized in either surgery plus adjuvant chemotherapy or surgery alone would make this distinction possible. However, this causes ethical dilemmas because chemotherapy would be withhold in patients who might actually benefit. Yet, a solid response assessment per subtype is necessary for implementation in clinical decision-making. We therefore propose to treat patients with two neoadjuvant and two adjuvant courses of CAPOX and determine the response in tumor resected specimens.

Applying neoadjuvant chemotherapy may have several advantages: the possibility of response monitoring, early eradication of micrometastases and more complete resections. Neo-adjuvant treatment is already standard of care for different GI malignancies including esophageal, gastric and rectal cancers [3–7]. The FOxTROT Collaborative Group (2012) was the first to set up a neoadjuvant trial in patients with locally advanced resectable colon cancer and concluded that preoperative chemotherapy is feasible with acceptable toxicity and perioperative morbidity [8]. After this pilot study, they conducted a randomized phase 3 trial investigating the effect of neoadjuvant chemotherapy in patients with a cT3–4 N0-2 M0 colon cancer. Patients were randomized 2:1 between 6 weeks of neoadjuvant combined with 18 weeks of adjuvant FOLFOX/CAPOX or 24 weeks of adjuvant FOLFOX/CAPOX. Neoadjuvant chemotherapy was safe with less major surgical complications, significant down-staging and a reduced risk of incomplete resection. Although the primary endpoint of the study (freedom from recurrent or persistent disease after 2 years) was not met, the risk of a recurrence after 2 years was reduced to 13.6% with peri-operative chemotherapy compared to 17.2% with adjuvant chemotherapy only (HR 0.75 (0.55–1.04), *p* = 0.08)) [9].

In the proposed study we will investigate the predictive value of the CMS classification on chemotherapy response in a neoadjuvant setting, including pathological response and radiological response and their correlation with RFS and OS. This allows us to determine therapy efficacy in individual patients and per subtype.

### Objective

The primary aim of this study is the evaluation of the pathological tumor response to neoadjuvant systemic chemotherapy per CMS in patients with MSS high risk stage II and stage III colon cancer.

## Methods

### Study design

CONNECTION II is a prospective, multicenter interventional cohort study that will be performed as a substudy of the Prospective Dutch ColoRectal Cancer cohort (PLCRC). PLCRC is a nationwide cohort study of the Dutch Colorectal Cancer Group (DCCG), facilitating scientific research to improve the outcome and quality of life of patients with colorectal cancer [10]. We aim to include patients in 8–10 Dutch hospitals that participate in PLCRC.

In CONNECTION II patients with a MSS cT3–4NxM0 colon tumor will be treated with two courses of neoadjuvant and two courses of adjuvant capecitabine and oxaliplatin (CAPOX) (Fig. 1 and Table 1). The CMS classification will be determined on both the pre-treatment biopsies and the resection specimen. At least 4 multi-region biopsies will be taken pre-treatment to ensure a sample with vital tumor and sufficient RNA quality. Tumor response will be assessed on the resection specimen using the tumor response grading (TRG) system as proposed by Dworak et al. [11]. Radiological response evaluation will be centrally performed by dedicated radiologists on sequential CT scans made at baseline and after two courses of neoadjuvant chemotherapy but before resection. Pathologists and radiologists will be blinded for the CMS classification.

**Fig. 1 Fig1:**
[figure not shown]
Flow diagram of clinical study. *Patients with an MSI tumor will be excluded from this study. ** At 4 time points blood samples will be collected for ctDNA analyses and future biomarker studies

**Table 1 Tab1:** Study flowchart of clinical study

Study procedures	Inclusion	Neo-adjuvant Chemotherapy							Surgery				Adjuvant Chemotherapy						Follow up			
*week*	< 0	1	2	3	4	5	6	7	8	9	10	11	12	13	14	15	16	17	18	19	20	21
Check in- and exclusion	x																					
Sign Informed Consent	x																					
Blood withdrawal for ctDNA + plasma	*x* ^*a*^							*x* ^*b*^				*x* ^*c*^									*x* ^*d*^	
CT-scan	x							*x* ^f^														
Surgery									x^g^													
CAPOX		*C1D1*			*C2D1*								*C3D1* ^*e*^			*C4D 1*						
Record medical history	x	x			x								x			x						
Document concomitant medication/therapies	x	x			x								x			x						

^a^: blood withdrawal may be done at screening or immediately before cycle 1 day 1

^b^: blood withdrawal to be performed after cycle 2 week 3 and before surgery

^c^: blood withdrawal to be performed before cycle 3 day 1

^d^: blood withdrawal to be performed approximately 12 weeks after surgery

^e^: Cycle 3 day 1 should ideally start within 4–8 weeks after surgery, at the latest: 12 weeks after surgery

^f^: CT should be performed after completion of cycle 2 and before surgery

^g^: Surgery should ideally be performed 7–9 weeks after Cycle 1 day 1, but has to be performed 11 weeks after Cycle 1 day 1

Optionally, blood samples are taken for circulating tumor DNA (ctDNA) analysis and plasma storage at four time points: at baseline, after neoadjuvant treatment, after surgery and after completion of the adjuvant chemotherapy. Follow-up will be performed until 10 years post-surgery. Data on local recurrences, metastases and survival will be documented.

### Study population

Patients diagnosed with resectable cT3–4NxM0 colon cancer are eligible for the CONNECTION II trial. Baseline CT-scans of all patients will be reviewed by dedicated radiologists in the treating hospitals with special focus on tumor staging. MSI status will be determined on biopsy material to exclude patients with an MSI tumor [12].

Patients are eligible when they meet the following criteria:
Able and willing to provide written informed consent for the CONNECTION II studyInformed consent signed for PLCRC components ‘clinical data’ and ‘future studies’MSS based on pre-treatment biopsy by immunohistochemistry (IHC)Fit to undergo neoadjuvant chemotherapy with capecitabine + oxaliplatin and subsequent surgery judged by the primary treating physicianAdequate bone marrow, liver and renal function

Patients will be excluded if any of the following criteria are met:
Any other malignant disease within the preceding 5 years apart from non-melanotic skin cancer, carcinoma in situ and early stage disease with a recurrence risk of less than 5%Colonic obstruction that cannot be defunctioned by a stomaPregnant or lactating women

### Main study parameter/endpoint

The primary endpoint is the pathological tumor response to neoadjuvant chemotherapy per CMS. The pathological response will be centrally scored on HE-stained slides from the resection specimen using the tumor response grading system according to Dworak [13, 14]. Based on results from the FOxTROT study, a good response will be defined as TRG2, TRG3 or TRG4; poor response as TRG1 or TRG0. The CMS classification will be determined on the pre-treatment biopsies and on the resection specimens. RNA will be isolated from FFPE material and analyzed on the nCounter SPRINT profiler, a reliable and robust platform for samples with degraded RNA such as FFPE samples [12, 15, 16].

### Secondary study parameters/endpoints

Additional pathological markers to assess the tumor response: the modified Ryan scheme (TRS) [13] and expression of Ki-67 and Caspase-3 and morphological cytostatic-cytotoxic effects on HE-stained tissue slides.Pathological response per TRG and TRS category separately for the different CMS subtypes.Radiological tumor response to neoadjuvant chemotherapy.Recurrence free survival (RFS) at two and three years. RFS is defined as the time elapsed between the diagnosis of the primary tumour and either the date of any recurrence of disease, time of death, or the date of the last follow-up visit at which a patient was considered to have no recurrence.Overall survival (OS) at five and ten years.Therapy-induced CMS differences.Prognostic and predictive value of cytotoxic lymphocytes (CytoLym) and cancer-associated fibroblasts (CAF) infiltration scores.Diagnostic accuracy of ctDNA measurements for monitoring treatment response to neoadjuvant treatment and detection of residual disease.Exploration of proteome profiles for monitoring treatment response to neoadjuvant treatment and detection of residual disease.Percentages of pathological complete (R0), pathological microscopic incomplete (R1) and pathologically macroscopic incomplete (R2) resections.Surgical complication rate (i.e. wound infections and anastomotic leak).

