#### Secondary study endpoints

Categorical data (pathological tumor response according to the Modified Ryan scheme) are compared using Chi-square analysis or Fisher’s exact test and are shown as numbers, relative and absolute rates. Continuous data (CytoLym and CAF infiltration scores, radiological tumor response, pathological response by percentage of Ki-67 and Caspase-3 positive neoplastic cells) are compared using non-parametric T-test or Mann-Whitney U test where appropriate and are shown as mean and standard deviation or median and interquartile range (25–75%). *P*-values are two-tailed and results < 0.05 are considered significant.

The OS at 5 and 10 years and RFS at 2 and 3 years will be calculated and depicted by means of the Kaplan Meier technique and will be compared using the (stratified) logrank test. Hazard ratios and 95% confidence intervals will be calculated with a (stratified) cox-proportional hazard analysis. The RFS will be analyzed per CMS subgroup, per TRG and radiological response. All estimates will be accompanied by 95% confidence intervals.

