### Adverse events

The treatment with CAPOX in this study is standard of care, therefore AE and SAE are not expected to be different. As both the treatment with CAPOX and the surgery are part of the standard of care, only two specific SAEs are defined which are possibly related to the adjusted study schedule. Information will be collected on patients who prematurely stop chemotherapy treatment and of patients who are not able to undergo planned surgery due to progressive disease/obstruction.

The following two SAEs will be reported:
If the surgery has to be postponed for more than 8 weeks after the start of cycle 2 of CAPOX.If patients can not complete all the neoadjuvant chemotherapy courses.

The study coordinator will report these SAEs to the accredited Institutional Review Board (IRB) that approved the study protocol.

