This makes it impossible to know whether patients with the poor-prognosis subtype (CMS4) have an impaired survival due to the aggressive nature of the tumor or due to a limited response to chemotherapy. Therefore, it is unknown whether these patients should receive chemotherapy or not. This also holds true for the other subtypes. Although CMS1–3 show superior outcomes to CMS4, it is unknown whether this is due to a favorable tumor biology or due to a substantial response to chemotherapy. We therefore believe that a solid chemotherapy response assessment per subtype is an important and essential step to distinguish between prognosis and prediction, and to incorporate the CMSs in clinical decision-making.

Administering neoadjuvant chemotherapy in the suggested study population was proven safe and feasible in the FOXTROT study [8, 9]. Importantly, the pathological tumor response was evidently associated with recurrence free survival. Patients with a complete response (TRG4) developed no recurrences after 5 years of follow-up, compared to 26% of patients that showed no regression at all (TRG0) [9]. This illustrates that the response to chemotherapy of the primary tumor may indeed be a reliable measurement for chemotherapy efficiency.

The primary endpoint of the proposed study is the pathological tumor response, which will be centrally scored using the TRG by Dworak, a highly reproducible scoring system which is often used and clinically meaningful [11]. Evidently, tumor response monitoring using histology requires invasive procedures. As a secondary endpoint, radiological response will be scored by a central board of radiologists and compared to the pathological tumor response to evaluate this noninvasive technique as a response modality. Both the histological and radiological response will be correlated to RFS and OS to assess their prognostic value.

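### RFS runs from diagnosis but counts only recurrence and death, so local progression that prevents resection and R2 residual tumour are not clearly events when they occur

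*Protocol article*

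**What the plan says.** The protocol article, under Secondary study parameters/endpoints, defines RFS as the "time elapsed between the diagnosis of the primary tumour and either the date of any recurrence of disease, time of death". A patient with neither event is followed to "the date of the last follow-up visit at which a patient was considered to have no recurrence". No other event is listed, and no other section redefines RFS or restricts it to resected patients.

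The protocol expects some patients never to become tumour-free. The Adverse events section collects information on "patients who are not able to undergo planned surgery due to progressive disease/obstruction". The secondary endpoints include the percentage of "pathologically macroscopic incomplete (R2) resections". Neither item is linked to RFS.

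Three further statements bear on the point:
- Study population: "Patients diagnosed with resectable cT3–4NxM0 colon cancer are eligible".
- Study design, text below Table 1: "Data on local recurrences, metastases and survival will be documented".
- Statistical analysis, Secondary study endpoints: "The RFS will be analyzed per CMS subgroup, per TRG and radiological response". The Discussion adds: "Both the histological and radiological response will be correlated to RFS and OS to assess their prognostic value".

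**The concern.** The time origin and the event list belong to different settings. In an adjuvant trial the clock starts after resection, and recurrence and death cover every way to fail. Here it starts at diagnosis with the tumour in place, and surgery ideally follows 7 to 9 weeks after the first chemotherapy cycle begins (Table 1, note g). A patient can fail in that window, or at surgery, without anything having recurred.

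The clear gap is local progression that prevents resection, and R2 residual tumour. If these failures are missed when they happen, RFS at 2 and 3 years tends to be too high. The comparison between groups can also be distorted if such failures are more common in some groups than in others. Unresected patients can enter the analyses by CMS and radiological response. They have no TRG, but R2 patients can enter all three analyses. The Discussion relies on these associations to judge the prognostic value of response.

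**Working it through.** The protocol gives no RFS event rate, power or sample size, so there is no figure of its own to reproduce. The check has two parts: the logic of the definition, then an illustration of scale.

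**How the definition treats each patient**
- Recurrence after R0/R1 resection, or death: an event. No problem.
- New metastasis before surgery in a patient who entered as M0: metastases are documented, so this may be coded as a recurrence. The text does not say.
- Local progression that prevents resection: not listed as an event.
- R2 resection: not listed as an event; reported only as a separate endpoint.

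The last two groups can be coded in three ways: (A) event-free until death or a later finding labelled recurrence; (B) censored at failure; (C) recorded by the assessor as recurrence. Coding C gives no bias. B is informative censoring, because the patients removed are those who have just failed.

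**Inputs.** All shares are assumptions.
- p, the affected share: 1%, 2% or 5%.
- r, the share of affected patients with a recorded event by 2 years: 75%, 50% or 25%.
- F, the true 2-year failure including the affected patients: 13.6% (2-year recurrence risk with peri-operative chemotherapy in the cited phase 3 trial) or 30% (upper end of the share developing metastases despite treatment). Both come from the Background and serve only as inputs.

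**Coding A.** Overstatement of 2-year RFS = p × (1 − r).
- 1% × 0.25 = 0.25 points
- 2% × 0.50 = 1.0 points
- 5% × 0.75 = 3.75 points

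**Coding B.** The unaffected patients fail at q = (F − p)/(1 − p), and Kaplan-Meier reads 1 − q. The overstatement is p(1 − F)/(1 − p).
- F = 13.6%: 0.01 × 0.864/0.99 = 0.87 points; p = 2% gives 1.76; p = 5% gives 4.55
- F = 30%: 0.01 × 0.70/0.99 = 0.71 points; p = 2% gives 1.43; p = 5% gives 3.68

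**Effect on a contrast.** Assume true failure of 25% v 15%, a 10-point difference, with r = 50% in A.
- Affected 5% v 1%: A gives (25 − 2.5) − (15 − 0.5) = 8.0; B gives 20/0.95 − 14/0.99 = 21.05 − 14.14 = 6.9
- Affected 3% in both: A gives 23.5 − 13.5 = 10.0; B gives (22 − 12)/0.97 = 10.3
- Affected 1% v 5%: A gives 24.5 − 12.5 = 12.0; B gives 24/0.99 − 10/0.95 = 24.24 − 10.53 = 13.7

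The contrast shrinks, holds or grows, depending on where the affected patients lie.

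**One patient in a subgroup.** The planned sizes are 35 in CMS3, 209 × 0.35 ≈ 73 in CMS4 and 209 × 0.49 ≈ 102 in CMS2. One miscoded R2 patient moves the crude rate by up to 100/35 = 2.9, 100/73 = 1.4 and 100/102 = 1.0 points.

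**The case against.** The strongest reply is that this is one sentence on a secondary endpoint in a condensed article. Analysis populations and coding rules commonly sit in the full protocol or SAP. The data are also largely collected already: R status is an endpoint and lost surgery is recorded. That lowers the cost and the severity, but it does not remove the point. The article gives a complete definition with a stated origin and an event list, and following it as written delays or loses real failures.

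Some stronger readings are tempting but unsupported:
- A reader might infer that all progression before surgery escapes RFS. New metastases in patients enrolled as M0 may already count as recurrence.
- A reader might infer that RFS must be biased upward. The censoring clause fits a patient with known tumour poorly, and an assessor could record the failure as recurrence. The bias is a tendency.
- A reader might infer that the association with response is necessarily weakened. Progression on chemotherapy plausibly concentrates in non-responders, which would weaken it, but the reverse imbalance exaggerates it and an equal share leaves it nearly unchanged.
- A reader might apply the affected share to the 209 patients of the sample size section. Those are sized for a response scored on the resection specimen, so unresected patients cannot be among them; R2 patients can.

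Sampling error is also larger than most of the illustrated effects. At 13.6% failure the 95% half-width is 1.96 × √(0.136 × 0.864/209) ≈ 4.6 points with 209 patients and about 11 with 35. For 25% v 15% in 73 v 102 patients it is 1.96 × √(0.1875/73 + 0.1275/102) ≈ 12 points. This limits the practical weight, although a systematic error does not average out as sampling error does.

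**Conclusion.** The point holds as a badly fixed definition of a secondary endpoint, of minor to moderate severity. With the origin at diagnosis, local progression that prevents resection and R2 residual tumour are not clearly events at the time of failure. Whether they count depends on how assessors happen to code them.

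The likely direction is overstated 2- and 3-year RFS. Under the assumed inputs this is 0.3 to 3.8 points if patients are carried as event-free and 0.7 to 4.5 points if they are censored at failure. It is zero if no patient is affected or if all are coded as recurrence. The true size is unknown, because the protocol gives no rate of lost resection or R2, and it is probably small in a resectable M0 population. Distortion between groups needs unequal shares, which the protocol neither shows nor rules out. The primary endpoint, the sample size and OS are unaffected.

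**What to change.** In Secondary study parameters/endpoints, define the endpoint as time from diagnosis to the first of:
- progression, local or distant, that precludes planned resection (date documented);
- R2 resection (date of surgery);
- recurrence after R0/R1 resection;
- death from any cause.

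Censor all other patients at the last visit free of these. Event-free survival would be a fitting name. It would also bring the endpoint closer to that of the phase 3 trial described in the Background, which counted persistent as well as recurrent disease.

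Use this version for the analysis by CMS. For groups that become known only after baseline, start the clock when the group is known:
- TRG: from surgery, with R2 as an event at surgery.
- Radiological response: from the post-cycle-2 CT, with a sensitivity analysis that excludes progression diagnosed on that same CT, since one scan would otherwise supply both group and outcome.

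Record progression separately from obstruction, with its date; the Adverse events section now collects them together.

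The cost is a few sentences and one data item: the reason surgery was lost and its date. R status is already collected. The reported rate will be slightly lower, and the name will differ from the RFS usual in adjuvant trials.
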